### Analysis

2.9

#### Aim 1

2.9.1

We assess acceptability by determining what proportion of peers can conduct the screening outreach intervention; we will assess fidelity based on which aspects of screening were completed. During audit and feedback meetings with peers, we will assess ease and barriers to implementing the screening as intended. We will descriptively examine patterns of reach and acceptability within the rural population served.

As part of the implementation evaluation of Aim 1, clinic study investigators will review positive screens and subsequent testing results (i.e., echocardiography has been performed, and whether the echocardiogram reveals structural heart disease).

#### Aim 2

2.9.2

We hypothesize that participants assigned to the intervention group will experience a higher proportion of linkage to cardiology care at 2-months (primary outcome). We will test statistical imbalance between the intervention and control groups on baseline demographic characteristics; those showing significant imbalance will be included as covariates in the primary outcome model. Linkage to cardiology care at 2-months, the primary outcome, will be analyzed with a generalized estimating equation (GEE) model with binomial family and logit link, which allows us to control correlation introduced by peer site. Missing data is imputed as not retained, and robust standard errors will be used for hypothesis tests.

Secondary outcomes will be tested using GEE models with appropriate distributions and link functions; we test hypotheses of within- and between-group changes over time (screening, 2, and 6 months), comparing the intervention to EUC. Missing secondary outcome data will be handled using multiple imputations if missing at random is a reasonable assumption, single imputation if missing not at random. Sensitivity analyses will be carried out to evaluate the impact of missing data.

Details on the sample size justification, including assumptions about baseline rates and detectable effect sizes, are provided in Section 2.4. Sample size and power.

#### Aim 3

2.9.3

For Aim 3, we will analyze qualitative data from focus groups and individual interviews using thematic analysis to identify key barriers and facilitators to implementing the peer-assisted telecardiology model. Following standard qualitative procedures, including codebook development and iterative coding, this analysis will focus on contextual factors, perceived value of the intervention, and considerations for scale-up and sustainability in rural settings. Particular attention will be paid to implementation strategies, adaptations across sites, and stakeholder-reported challenges and successes. Data will be managed and coded using ATLAS.ti.

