### Overview of the study design

2.1

The PEER-Heart study is a hybrid type 1 effectiveness-implementation trial (Curran et al., 2012), which simultaneously evaluates the clinical effectiveness of an intervention while gathering data on implementation processes and contextual factors to inform future scale-up. This dual focus allows researchers to explore not only the peer-facilitated telecardiology intervention compared with enhanced usual care but also factors that influence its implementation among people who use methamphetamine in rural areas. The study aims to:•Aim 1. Adapt and implement a peer-directed MAHF screening program and assess its feasibility and acceptability for people with MAU living in rural communities. The study will assess how well peers are able to conduct the screening, identify barriers and facilitators to implementation, and examine disparities in reach across demographic groups**.**•Aim 2. Determine feasibility, acceptability, and effectiveness of a novel peer-assisted telecardiology program to screen and engage patients at risk for MAHF in cardiology care at 2 months. This study is a non-blinded, two-arm, randomized controlled trial to test the superiority of peer-assisted telecardiology in comparison to enhanced usual care (EUC) for heart failure treatment in people who use methamphetamine in rural areas of Oregon (clinicaltrials.gov NCT06461962).•Aim 3. To identify and characterize facilitators and barriers to implementation. Using individual interviews and focus groups during Aim 1 study activities, we seek to identify and understand strategies for scaling and sustaining the PEER-Heart model in other settings.

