**Feasibility and Acceptability Assessments*****(intervention arm only)***	Weiner et al., 2017 – AIM (Acceptability of Intervention Measure)	Acceptability of peer-delivered telecardiology support: approval, appeal, liking, welcome	4	Likert

Management of identified cardiovascular disease will be based on clinical practice routine and to the discretion of treating clinicians. Time to diagnostic evaluation, including echocardiography, may vary across participants and study arms. Participants in the EUC arm receive care consistently with local standard practices, and equipoise is maintained because local providers may navigate logistical or system-level hurdles as efficiently as the telecardiology team. The study does not restrict participants’ access to any diagnostic testing or treatment.

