#### Implementation assessment

2.8.3

Additionally, the study will assess implementation outcomes such as the feasibility and acceptability of peer-assisted MAHF screening, barriers and facilitators to implementing telecardiology care, and drivers of intervention effectiveness, maintenance, and sustainability using the RE-AIM (reach effectiveness adoption implementation maintenance) framework.

We will evaluate implementation and barriers by conducting focus groups consisting of 15 peers from participating community-based organizations and clinicians both involved and not involved in the project during the first and third year of the study, exploring formative feedback and tele-cardiology intervention factors. Additionally, individual qualitative interviews will be conducted with 15 participants in each group (total N = 30) to explore the screening intervention and linkage to cardiology care within the client-peer relationship. All interviews and focus groups will take place in convenient, private, and safe settings, either in-person or virtually.

To carry out the analysis the team will employ thematic analysis to create a coding scheme, practice coding, and revise iteratively, following common qualitative study practices (Braun and Clarke, 2006). Qualitative analysts will complete line-by-line coding of five sample transcripts independently, discuss transcript coding, reach a consensus about code definitions, and finalize a codebook (of all codes and their definitions). We will review a sample of transcripts to ensure reliable coding, assess the need for new codes, or revise existing code definitions. We will hold weekly meetings to discuss the coding process, resolve problems, ensure consistency, and adjust the interview guide or sample as needed. The team will read for negative cases (i.e., cases that do not fit themes) and will conduct a member check at each site. We will use qualitative analysis software (ATLAS.ti) for data management and analysis.

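### Aim 1 acceptability is measured as the share of peers able to deliver screening, a quantity that does not respond to whether people accept or refuse the screen

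*Protocol article*

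**What the plan says.** All references are to the protocol article.

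- **Section 2.1, Aim 1.** The study will adapt and implement peer-directed screening and "assess its feasibility and acceptability for people with MAU living in rural communities". Peer performance comes next, as a question of its own: "The study will assess how well peers are able to conduct the screening".
- **Section 2.8.3.** The implementation outcomes include "feasibility and acceptability of peer-assisted MAHF screening".
- **Section 2.9.1.** The measure is then fixed: "We assess acceptability by determining what proportion of peers can conduct the screening outreach intervention". The same sentence goes on: "we will assess fidelity based on which aspects of screening were completed". The paragraph closes with: "We will descriptively examine patterns of reach and acceptability within the rural population served".
- **Table 1, last row.** The acceptability scale is described as "Acceptability of peer-delivered telecardiology support: approval, appeal, liking, welcome". The row is limited to the intervention arm, and the table covers the 2- and 6-month follow-up surveys.
- **Section 2.8.3, interviews.** The plan is that "individual qualitative interviews will be conducted with 15 participants in each group (total N = 30"). The topics include the screening intervention.
- **Section 2.5.** Only people who screen positive and consent become study participants.

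**The concern.** Acceptability to the people offered a test and ability of staff to deliver it are different properties. Section 2.1 keeps them apart; section 2.9.1 gives the name of the first to the second. A programme in which every peer can run the fingerstick, ECG and questionnaire would score full marks on the stated measure whether most people offered the screen took it or declined it.

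Acceptability is a headline claim in the Abstract, section 2.1 and the Discussion, and it supports the case for scale-up. The Background and Discussion name stigma and mistrust as the barriers that peers are meant to overcome. Refusal is the most direct way in which those barriers would show, and the stated measure does not register it.

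**Working it through.** The plan gives no target or expected value for acceptability, so there is no figure to reproduce. The check compares the definition with the objective, and then asks whether another stated measure fills the gap.

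**Step 1: objective against measure.**

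| | Aim 1 objective (2.1) | Stated measure (2.9.1) |
|---|---|---|
| Whose response | People who use methamphetamine | Peers |
| What is asked | Whether the screening is acceptable to them | Whether the peer can carry it out |
| Denominator | Not stated | Peers |

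The measure answers the peer-performance question that section 2.1 lists separately.

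**Step 2: other stated sources.**

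- *Fidelity (2.9.1)* records which parts of the screen were completed. It informs on completion by component once a screen is under way, but does not count people who decline at the outset.
- *Descriptive look at the population served (2.9.1)* has the right population, but no numerator, denominator or instrument is attached.
- *Acceptability scale (Table 1)* rates telecardiology support in the intervention arm, not screening.
- *Participant interviews (2.8.3)* cover screening, but with enrolled people, who by section 2.5 had already accepted it.
- *Audit and feedback meetings (2.9.1) and focus groups with peers and clinicians (2.8.3)* can report refusals second-hand, without a rate.

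**Step 3: does the measure move with refusal?** Let P be the number of peers, C the number able to conduct screening, S the number of people screened and A the number offered screening.

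- Stated measure = C / P
- Uptake = S / A; refusal = 1 − S / A

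Neither S nor A appears in C / P. Section 2.4 gives S as at least 220. The document does not give A, so the values below are assumptions that only show the range.

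| A (assumed) | Uptake = 220 / A | Refusal | Highest possible C / P |
|---|---|---|---|
| 300 | 73% | 27% | 100% |
| 440 | 50% | 50% | 100% |
| 550 | 40% | 60% | 100% |
| 1,100 | 20% | 80% | 100% |

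The last column is constant by construction. The table illustrates that insensitivity; it does not forecast uptake.

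**The case against.** The strongest reply is that the peer proportion is not the whole plan. Section 2.9.1 also promises a population-level description of reach and acceptability, and an article may leave its detail to the full protocol. The screening instruments are in an appendix that is not shown, and Table 1 lists follow-up measures only, so absence from it does not prove that nothing is collected at screening. A log of approaches is routine and may exist. Peers can also report refusals in their meetings and focus groups.

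Most of this stands, and it limits the point. A reader might infer that low uptake would go unseen, or that no screening acceptability data exist at all; the document does not support either. A reader might also infer that, without a count of people approached, differences in reach across demographic groups cannot be examined. That is not so: section 2.2 gives a client profile (over 1,500 served in 12 months, 88% aged 25 to 64, 74% White, 59% male) with which those screened could be compared. That comparison shows who was reached, although it cannot separate refusing from never being asked.

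The reply does not rescue the definition. The article does not merely omit a measure; it states one, and the one stated belongs to a different construct.

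It is also fair to say that completed screens over offers is a behavioural measure that overlaps with reach, that the $5 payment for completing the screening assessments (section 2.10) may raise it, and that who counts as offered is hard to pin down when recruitment uses flyers and gatherings (section 2.5).

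**Conclusion.** The point holds as a mismatch between the Aim 1 objective and the measure fixed for it. The peer proportion is feasibility or adoption by peers, and it does not change with the refusal rate. The population-level sentence in section 2.9.1 softens the consequence but defines nothing that could replace it.

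The size cannot be given as a number, because neither the number of peers screening nor the number of people offered screening is stated. The insensitivity itself needs no assumed count. The conclusion rests on reading the 15 interviewees per group as members of the two study arms, and on section 2.9.1 being the operative definition.

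The effect is confined to the implementation findings on screening. Randomisation, the linkage outcome at 2 months, the sample size of 122 and the Aim 2 analysis are untouched. It is worth correcting while screening continues, since refusals that were not logged at the time cannot be reliably recovered.

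**What to change.** In section 2.9.1:

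1. Relabel the peer proportion as feasibility or adoption by peers.
2. Define acceptability of screening as completed screens divided by people individually offered screening, overall and by component (questionnaire, fingerstick BNP, ECG). Name this as the measure behind the population-level sentence.
3. Report the share of screen-positives who consent to randomisation.
4. Have peers keep a brief tally of offers and refusals, with a one-line rule for what counts as an individual offer, so that seeing a flyer or attending a gathering does not count.

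The cost is a paragraph of text and a small logging burden for peers. The numerator should already be traceable, since the symptom questionnaire is collected in REDCap (section 2.5) and completed screening assessments are paid for (section 2.10). Some imprecision in the denominator will remain under outreach recruitment and should be acknowledged when results are reported. Giving a reworded acceptability scale to everyone screened would be optional new data collection and is not needed to correct the definition.

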### Sample size and power

2.4

As part of Aim 1 and to reach enrollment goals, we plan to screen at least 220 individuals for elevated BNP levels, identifying people who use methamphetamine at risk for heart failure. This estimate reflects an initial screening target; however, the study is powered on the number of individuals who screen positive rather than the total number screened, and screening will continue as needed to enroll 122 participants with elevated BNP. We will continue screening as needed to reach our target enrollment. No prior study has reported the prevalence of positive screening (using BNP) for heart failure in community-dwelling people who use methamphetamine who are not already diagnosed with cardiomyopathy, however one prior cohort study with people who use methamphetamine presenting to the emergency department found that 63 % had abnormal BNP levels (Richards et al., 2018), which likely overestimates the prevalence in a community-dwelling population. In contrast, in the STOP-HF randomized controlled trial, approximately 40 % of community-dwelling primary care patients with cardiovascular risk factors had a BNP > 50 (Ledwidge et al., 2013), providing a more conservative reference point for BNP positivity in non-acute settings. Based on these findings, we anticipate that 122 individuals from those will have elevated BNP levels indicative of possible heart failure and meet other eligibility criteria, making them eligible for enrollment in the Aim 2 randomized controlled trial. Assuming a 10 % linkage to cardiology care in the enhanced usual care (EUC) arm, a sample size of 122 participants allows us to detect a clinically meaningful difference in linkage rates between study arms with adequate statistical power. So based on these considerations, this sample sizeallows detection of a 20 % increase in the linkage to cardiology care in the telecardiology arm (i.e., achieving a rate of 30 % at 2 months), assuming 80 % power for a two-sided test of proportions at α= 0.05. This baseline estimate is informed by linkage rates reported in symptomatic, hospitalized populations, which may differ significantly from outpatient screening populations, in whom follow-up care rates are expected to be lower.

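### Significance tests of baseline demographic imbalance choose the covariates for the primary model, so the model is not fixed in advance and precision is forgone

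*Protocol article*

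**What the plan says.** Section 2.1 describes a "non-blinded, two-arm, randomized controlled trial to test the superiority of peer-assisted telecardiology". For the primary outcome, linkage to cardiology care at 2 months, section 2.9.2 (Aim 2) specifies a "generalized estimating equation (GEE) model with binomial family and logit link, which allows us to control correlation introduced by peer site", with robust standard errors.

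The covariates come from a two-step rule in the same section. First, "We will test statistical imbalance between the intervention and control groups on baseline demographic characteristics". Second, "those showing significant imbalance will be included as covariates in the primary outcome model".

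The article names no covariate that is always included, and it does not confine the rule to a sensitivity analysis. It gives neither a significance level for the imbalance tests nor a list of the demographic characteristics. Section 2.5 shows that BNP, QRS width and heart failure symptoms are all recorded at screening, before randomisation.

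**The concern.** Under sound randomisation any baseline difference between the arms is due to chance, so a significance test of that difference answers no useful question. What makes a covariate worth including is its relation to the outcome, and the rule never looks at that. A demographic variable unrelated to linkage enters if it happens to be imbalanced, and one strongly related to linkage stays out if it happens to be balanced. Measures that are not demographic are not eligible at all.

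The logit link adds a second problem. The odds ratio is non-collapsible: conditioning on a prognostic covariate changes the quantity being estimated, even when that covariate is balanced. The odds ratio that the primary analysis targets is therefore unsettled until someone has compared the arms, in a trial that is not blinded. At stake are a prespecified primary estimate and the precision that adjustment for a useful baseline variable would bring.

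**Working it through.** **Inputs.** From section 2.4: linkage of 10% under enhanced usual care and 30% under telecardiology, 122 participants, two-sided α of 0.05, 80% power. Assumed, because not stated: 1:1 allocation (61 per arm), imbalance tests at 0.05, independent tests, and 5 or 10 demographic variables as illustrative counts.

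**1. The plan's own sample size.** Two proportions, pooled variance under the null, p̄ = 0.20:

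n per arm = [1.960·√(2·0.20·0.80) + 0.842·√(0.10·0.90 + 0.30·0.70)]² / 0.20² = (1.109 + 0.461)² / 0.04 ≈ 61.6, so 62 per arm and 124 in total.

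The unpooled formula gives 118 and the arcsine formula 120. The stated 122 is reproduced within 2 participants, and 61 per arm gives 79.6% power. The calculation is for an unadjusted test of proportions.

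**2. How often chance alone changes the model.** With k independent tests at 0.05, P(at least one covariate enters) = 1 − 0.95^k:

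- k = 3: 1 − 0.857 = 14%
- k = 5: 1 − 0.774 = 23%
- k = 8: 1 − 0.663 = 34%
- k = 10: 1 − 0.599 = 40%

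Any one eligible predictor, however strong, enters with probability 5%. For BNP, QRS width and symptoms the probability is zero.

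**3. Expected events.** 61 × 0.10 + 61 × 0.30 = 6.1 + 18.3 = 24.4 linkages.

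**4. What the rule does to error and power.** Simulation with 61 per arm, a logistic model, and one standard normal prognostic covariate among 5 tested variables (t-tests at 0.05), 4,000 runs per scenario. Type I error used 20% linkage in both arms; power used 10% v 30%.

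| Assumed covariate log-OR per SD | 0.5 | 1.0 | 1.5 |
|---|---|---|---|
| Power, no adjustment | 80.8% | 79.8% | 79.3% |
| Power, protocol's rule | 80.5% | 80.0% | 79.5% |
| Power, covariate fixed in advance | 81.8% | 83.9% | 87.1% |
| Forgone by the rule (points) | 1.3 | 3.9 | 7.6 |
| Type I error, protocol's rule | 4.3% | 4.2% | 4.0% |
| Type I error, covariate fixed in advance | 4.4% | 4.8% | 4.4% |

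The simulation used model-based standard errors and no clustering by peer site, so it indicates direction and rough size only. On these figures the rule performs like no adjustment at all.

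**The case against.** The strongest reply is that the rule does little damage, and much of that reply stands.

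- **False positives.** A reader might infer that selecting covariates on the data inflates type I error because the standard error ignores the selection. The simulation does not support this: the rule gave 4.0% to 4.3%.
- **Planned power.** A reader might infer that the trial is underpowered. It was sized on an unadjusted comparison, and simulated power under the rule was 79.5% to 80.5%, essentially as planned. The loss is measured against a gain that the plan never claimed.
- **Overfitting.** With about 24 events, an unlisted set of covariates might seem risky. But the expected number entering by chance is only 5 × 0.05 = 0.25 or 10 × 0.05 = 0.5, and three or more would enter about 0.1% or 1.2% of the time. Overfitting is not shown.
- **Site.** It might seem that site is ignored. It already enters through the GEE correlation structure. County of residence might also count as demographic, since the characteristics are not itemised.
- **Known predictors.** Nothing in the article shows that BNP, QRS width or symptoms predict completing a cardiology visit. Section 2.5 itself notes that positive screening findings can be non-specific. That they are prognostic is a plausible assumption only, and the upper end of the assumed range (1.5 per SD) has no support in the document.

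Nor can the point be left to an analysis plan that is not shown. Such a plan could list the characteristics and state a test level, but it could not remove the selection rule without departing from the published text. None of these replies gives a reason to choose covariates by imbalance tests.

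**Conclusion.** The point holds as a weakness of method in the confirmatory analysis. It is not a threat to the validity of the test. The primary model and its conditional odds ratio are not fixed in advance, and the rule recovers almost none of the precision that a prespecified prognostic covariate would give.

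The chance that the model changes at all is 23% with 5 variables and 40% with 10, given independent tests at 0.05. The level and both counts are assumptions. The forgone power is about 1 to 8 points for an assumed log odds ratio of 0.5 to 1.5 per SD, and less if the covariate is weaker. The figure of 24 events also assumes 1:1 allocation. This should be corrected, but it does not call the planned sample size into question.

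**What to change.** Delete the imbalance tests as a selection rule. In their place, name one or two covariates measured before randomisation that are expected on prognostic grounds to relate to linkage, and keep them whatever the observed balance. Continuous log BNP and presence of heart failure symptoms at screening are workable examples. Leave peer site handled as planned, and present baseline characteristics by arm descriptively.

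Three details matter:

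- **Number.** With about 24 events, treatment plus two covariates gives 24.4 / 3 ≈ 8 events per term, so the list should stay short.
- **Form of BNP.** It should not be split at 50 pg/ml. Section 2.4 speaks of enrolling 122 participants with elevated BNP, whereas section 2.5 admits a positive screen on any of three criteria. On the first reading the split could be constant, and on either reading it discards information.
- **Symptoms.** Presence at screening is documented in section 2.5. A baseline symptom score is not: the KCCQ-based items in Table 1 are listed for the 2- and 6-month surveys.

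The cost is a change of analysis wording, with no new data and no change to the planned 122. The covariates must be chosen before outcome data are seen, and the gain in precision will be small if they turn out to be weakly prognostic.

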### Study setting

2.2

This study takes place in two rural counties, Coos and Curry, on the Southern Oregon Coast as a collaboration between local community partner Bay Area First Step (BAFS) and Oregon Health & Science University (OHSU) in Portland, Oregon. These counties are highly rural, with more than 98 % and 100 % of their territory, respectively, classified as rural (Census.gov | U.S. Census Bureau Homepage, 2025). Coos County has a population density of ~39 persons/sq mi, while Curry County is even more sparsely populated at ~13 persons/sq mi (Census.gov | U.S. Census Bureau Homepage, 2025). These characteristics contribute to limited healthcare infrastructure and access in both areas.

BAFS is a peer-led community-based service organization that provides housing and peer-delivered services designed to support PWUD and their families in these rural counties. BAFS leadership and staff contributed to the design of the intervention providing input on study procedures, recruitment strategies and feasibility within the local service context. BAFS plays an active role in the community and fosters strong relationships with potential study participants. In the past 12 months, BAFS has served over 1500 individuals, the majority of whom (88 %) were between the ages of 25 and 64. Most clients identified as White (74 %) and male (59 %), although BAFS also reaches a diverse population. BAFS has prior experience implementing and recruiting participants for new service and research initiatives, supporting the feasibility of achieving the proposed sample size. BAFS peers will recruit, screen, and link eligible individuals to care. Two BAFS peers have been trained and serve as research assistants, collecting participant consent and survey data.

In Oregon, to be certified as a peer, individuals must be older than 18 years, successfully complete an Oregon Health Authority approved training program and pass a criminal history background check. Depending on the specialization, training is 40 h for Peer Support Specialists (PSS), or 80 for Peer Wellness Specialists (PWS) and includes essential skills for peer support, person-centered communication techniques, and a range of other key competencies and guiding principles. Oregon requires recertification every three years and peers must complete a minimum number of hours, depending on the certification, of continuing education.

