### Study participants

2.3

The PEER-Heart study recruits individuals who are residents of Coos and Curry Counties, Oregon—the BAFS service area. As this is a feasibility study conducted within existing community-based services, participants will be recruited without predefined targets for gender or race/ethnicity, and enrollment is expected to reflect the demographics of individuals accessing participating sites.

Individuals meet the following inclusion criteria: age 18 years or older, active health insurance, self-report of any MAU in last 30 days and regular use over the prior year, no client-reported diagnosis of heart failure, and able to communicate in English. We exclude individuals who report existing engagement in medical care for heart failure and/or are actively taking medications specifically prescribed for the treatment of heart failure. The study excludes prisoners and detained individuals.

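### The primary GEE clusters its robust variance on an unstated number of peer sites; with fewer than about 10, as the setting suggests, it fails either its 5% level or its 80% power

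*Protocol article*

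**What the plan says.** Section 2.9.2 (Aim 2) of the protocol article analyses the primary outcome, a completed cardiology visit by two months, with a "generalized estimating equation (GEE) model with binomial family and logit link, which allows us to control correlation introduced by peer site". The next sentence reads: "Missing data is imputed as not retained, and robust standard errors will be used for hypothesis tests". So the clustering unit and the type of variance estimator are both chosen. No small-sample correction or reference distribution is named.

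On the number of clusters, section 2.2 says "This study takes place in two rural counties, Coos and Curry, on the Southern Oregon Coast", names one "local community partner Bay Area First Step (BAFS"), and adds that "BAFS peers will recruit, screen, and link eligible individuals to care". No section counts or defines a peer site. Section 2.3 has an open plural ("enrollment is expected to reflect the demographics of individuals accessing participating sites"). Sections 2.8.3 and 2.9.3 also refer to sites in general terms, and section 2.8.3 mentions partner organisations in the plural when describing the focus groups.

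Section 2.7 randomises individuals who screen positive and consent. Section 2.4 sizes the trial at 122 for 10% versus 30% linkage, with 80% power in a two-sided test of proportions at 0.05. Site plays no part in that calculation.

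**The concern.** A sandwich variance clustered on site estimates the variance of the treatment effect from one score contribution per site. With K sites it carries roughly K-1 degrees of freedom, however many participants there are. When K is small the estimate is biased downward and very variable, and a normal reference ignores both problems. With two sites the variance rests on a single degree of freedom.

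This is the trial's primary superiority test. If the sites are few and nothing is corrected, a false claim of superiority is several times more likely than planned and the confidence interval is too narrow. If a correction is added later, the level is repaired but most of the planned power is lost. Individuals are randomised, so both arms occur within sites, and the comparison can be made within site without either penalty.

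**Working it through.** **Inputs from the protocol article.** N = 122, 10% control and 30% intervention linkage, two-sided alpha 0.05, 80% power (section 2.4); individual randomisation (section 2.7); logit GEE by peer site with robust standard errors (section 2.9.2). **Assumed, because not stated:** 1:1 allocation (61 per arm), number of sites K, equal-sized sites, modest site variation (intraclass correlation 0.05, with 0 as a check).

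**Step 1: reproduce the stated sample size.** With pooled variance and no continuity correction, n per arm = [1.96·√(2·0.20·0.80) + 0.8416·√(0.10·0.90 + 0.30·0.70)]² / 0.20² = (1.109 + 0.461)² / 0.04 = 61.6, so 62 per arm or 124 in total. The stated 122 is within two participants, and 61 per arm gives 79.6% power. The figure is sound for a simple comparison of two proportions.

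**Step 2: size of the uncorrected robust test, in closed form.** With K equal-sized sites the sandwich variance behaves like (K-1)/K times an unbiased variance on K-1 degrees of freedom. The Wald statistic is then about √(K/(K-1)) times a t variable on K-1 degrees of freedom, so

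P(reject under the null) ≈ P(|t(K-1)| > 1.96·√((K-1)/K)).

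For K = 2 the threshold is 1.96·√0.5 = 1.386, and P = 1 - (2/π)·arctan(1.386) = 39.8%. For K = 3 it is 1.600, and P = 1 - 1.600/√(2 + 1.600²) = 25.1%.

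**Step 3: simulation.** N = 122, individual randomisation across sites, logit GEE with working independence, sandwich variance by site. The null has 10% linkage in both arms; power is at 10% versus 30%. The corrected test multiplies the variance by K/(K-1) and refers the statistic to t(K-1).

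| Peer sites K | Threshold | Closed-form type I error | Simulated type I error, uncorrected | Simulated power, corrected |
|---|---|---|---|---|
| 2 | 1.386 | 39.8% | 38% | 16% |
| 3 | 1.600 | 25.1% | 24% | 30% |
| 4 | 1.697 | 18.8% | 17% | 42% |
| 6 | 1.789 | 13.4% | 13% | 59% |
| 10 | 1.859 | 9.6% | 8% | 66% |
| 15 to 20 | 1.894 to 1.910 | 7.9% to 7.1% | about 5-7% | not tabulated |

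The corrected test rejects a true null in about 4% of runs. Its power is low because the t critical value is 12.71 on 1 degree of freedom, 4.30 on 2, 3.18 on 3, 2.57 on 5 and 2.26 on 9, against 1.96.

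**Step 4: sensitivity.** The inflation does not depend on site correlation: with intraclass correlation 0 the uncorrected rates were 37%, 23%, 18% and 12% at 2, 3, 4 and 6 sites. Very unequal sites (correlation 0.05) raised them to 43%, 31%, 25% and 22%, and left the corrected test at 6-11%. A full GEE fit, independence or exchangeable, gave 41-44%, 20-23% and about 15% at 2, 4 and 6 sites. A bias-reduced sandwich with a normal reference still gave about 21%, 10-11% and 9%.

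**Step 5: the alternative.** A Mantel-Haenszel test stratified by site held 4-5% type I error and 77-80% power at 2 to 10 sites. A logistic model with site as a fixed effect and model-based standard errors gave 5.5%, 3.2% and 4.2% type I error at 2, 4 and 6 sites, in a simulation with 20% linkage in both arms.

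**The case against.** The strongest reply is that the article does not say how many peer sites there are. Recruitment in section 2.5 spans parks, community gatherings, recovery housing and healthcare facilities, and the references to sites are open plurals. A reader might infer from the two counties and single partner that the trial certainly has a handful of sites, and hence that its type I error is certainly far above 5%. The documents do not support that. A small count is the more natural reading, since 15 sites would leave about eight participants each (122/15), but it remains an inference. At 15 to 20 sites the problem largely fades.

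Second, the inflation needs an uncorrected sandwich with a normal reference. The article does not rule out a correction, and an analysis plan that is not shown may supply one. This stands for the type I error. It does not rescue the method when sites are few, because the corrected test falls well short of the 80% power in section 2.4.

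Third, allowing for site is a legitimate aim. Peers support both arms, and the Discussion expects the quality and consistency of care to vary between facilitators. A reader might infer that individual randomisation makes site irrelevant to the variance. That goes too far: if the treatment effect differs between sites, inference beyond these sites does involve site-level variation.

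Fourth, site dummies are not a universal remedy. In an ordinary logistic model with many small sites they distort the estimate: against a true log odds ratio of 1.35, the median was 1.63 at 20 sites and 1.86 at 30, with 27% and 41% of sites uninformative. This stands and shapes the fix.

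**Conclusion.** The concern holds, conditionally on the number of peer sites. Below about 10 sites, the site-clustered GEE with robust standard errors cannot deliver both properties that section 2.4 relies on. Uncorrected, its type I error is about 38% at 2 sites, falling to 8% at 10; corrected, its power is about 16% rising to 66%. With roughly 15 or more sites the uncorrected error is about 5-7% and the objection to the method is minor.

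The figures rest on N = 122, the article's own 10% and 30% rates, and the assumptions of 1:1 allocation, equal-sized sites and modest site variation. Very unequal sites make matters worse. What can be criticised on the text as it stands is that the clustering unit and variance type are fixed for the primary test without a site count, in a setting that points to few sites.

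**What to change.** - State in sections 2.2 and 2.9.2 what a peer site is and how many there are.
- If sites are few (below about 10), do not cluster the primary variance on site. Use a Mantel-Haenszel analysis stratified by site or county, or a logistic model with site or county as a fixed effect and model-based or participant-level robust standard errors.
- If sites prove numerous (about 15 or more), the site-clustered GEE may stay with a named small-sample correction and reference distribution. A stratified or conditional analysis is the alternative; site dummies in an ordinary logistic model should be avoided there.
- For a count in between, prefer the stratified analysis, which still held its level and power at 10 sites.

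The cost is a change of analysis wording, made before outcomes are compared by arm. It needs no new data and no larger sample. The downside is that inference becomes conditional on the participating sites, which should be said when results are generalised.
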